#### Caregiver burden

Burden will be measured using the Zarit Burden Interview (ZBI) which is a 22-item validated self-report questionnaire developed to examine subjective burden of caregivers of people with dementia. The scale uses a five point Likert scale – ranged from never to nearly always present – to score every question. The final score is ranged between zero (low burden) to 88 (high burden). A validated Dutch and French version for use in Belgium is available [20, 21].

#### Health related quality of life of the caregiver

Health related quality of life will be measured using the EQ-5D-5 L. The EQ-5D-5 L is a valid extension of the 3-level questionnaire. It can be defined as a standardized non-disease specific value-based instrument to describe and value health related quality of life. The instrument consists of five health related domains (mobility, self-care, daily activities, pain, and depression/anxiety) to which a score from one to five can be given. Each score indicates the degree of perceived problems with the domain. Based on this score Quality Adjusted Life Years (QALYs) can be obtained for the cost-effectiveness analysis [22, 23]. Validated Dutch and French versions for Belgium are available as well as a valid telephone interviewing script in both languages.

#### Frequency of problematic behaviors and reactions of caregivers

To measure frequency of problematic behaviors in the care-recipient and the reaction of caregivers to these problems, the Revised Memory and Behavior Problems Checklist (RMBPC) will be used. This validated caregiver self-report measure contains 24 items including three domains (depression, memory-related problems and disruption) and two scales to be answered. One scale measures the frequency of problem behaviors of the recipient (five point scale from “never occurs” to “occurs daily or more often”) and the other measures the reactions of the caregiver to this behavior (five point scale form “not at all” to “extremely”). The described forward-back translation technique was used to translate the original English questionnaire into Dutch and French for Belgium [17].

#### Resource use and time spent in caregiving

Resource use of the care-recipient and also time spent in caregiving will be measured using the Utilization in Dementia instrument (RUD). This valid, standardized, and widely used instrument - available in Dutch and French for Belgium - can be used for collecting data on time spent in caregiving and resource use of dementia patients and their caregivers. To collect data on resource use of the person with dementia, caregivers only have to complete the part of the questionnaire measuring resource use of care-recipients [18].

Some small adjustments were made to measure resource use in order to better adapt the questionnaire to the Belgian context and to the setting of this trial. In contrast to the standard RUD questionnaire, amount of use of hospital admissions and care in a hospital emergency room will be asked for the last six months instead of over the last 30 days. Also, we added an additional table to the questionnaire containing the following respite services: day care (replaced from another table), night-time care (community-based or residential), short-stay, day sitting service, and in-home respite care (type Baluchon). For these respite services, potential use in the last six months will be asked. Additionally, a few Dutch words had to be changed to Dutch for Belgium [18].

Finally, information on potential use of other support will be collected separately by asking the caregivers if they currently receive any other supportive initiative for informal caregivers.

#### Intention to institutionalize the care-recipient into a long-term nursing home

The intention to institutionalize the care-recipient will be assessed using the Desire To Institutionalize scale (DTI) - originally developed by Morycz in 1985 [24] and slightly modified for use in the REACH II study [25]. Afterwards this modified version has also been validated by McCaskill et al. (2011) for use in different ethnical/racial groups [26]. This questionnaire contains six yes or no questions each measuring the caregiver’s desire to institutionalize the recipient into a nursing home, boarding home or assisted living. Because for this questionnaire no valid translations were available a forward-back translation method was used to translate the questionnaire in Dutch and French for Belgium.

#### Time to nursing home placement

Finally, the time to nursing home placement will be obtained by measuring the interval from the date of study enrollment to the date of permanent nursing home placement. Short term admissions in nursing home placements do not count as definitive nursing home placement. It is expected that even at 12 months a majority of patients will not be institutionalized. Hence, this parameter is to be considered as a secondary endpoint.

Additionally, the National Registration number of care-recipients will be obtained to allow us to trace study participants in the IMA database (Intermutualistisch Agentschap) and gather information on their date of placement in a nursing home over a longer time period than the trial.

#### Severity of dementia

Severity of dementia will be collected by using the Global Deterioration Scale (GDS) which is a valid and reliable instrument that distinguishes seven stages of dementia based on cognitive decline [27]. This questionnaire is not a neuropsychiatric test, but an instrument to objectively classify the severity of dementia. It can be administered by healthcare professionals and is often used in scientific research. A Dutch translation was available for the Netherlands. Two Belgian healthcare professionals were consulted to check appropriateness of this translation for the Belgian context. Also a French translation was made based on the original validated English version using the forward-back translation technique [28].

#### ADL functioning

Activities of Daily Living (ADL) of the care-recipient will be measured using a Belgian adapted version of the Katz Index of Independence in Activities of Daily Living [29]. The Belgian KATZ scale, which is an official instrument for mandatory use in Belgium, measures a person’s ability to perform activities of daily living based on a total score on six functions: bathing, dressing, toileting, transferring, continence, and feeding. Additionally, potential disorientation in time and place is asked in this questionnaire. In contrast to the original Katz index developed by Katz et al. [29] a score between one and four can be given for each domain of functioning. A score of four indicates total dependence (or total disorientation), while a score of one indicates total independence (no disorientation).

### Background characteristics

For caregivers we will obtain the following background characteristics: age, gender, region, marital status, ethnicity, educational level, relationship with the care-recipient, employment status, living situation, and time spent in caregiving. In both study groups the reason for (potential) use of respite will be asked based on evidence from the study of Connell et al. (2012) [30]. Earlier use of Baluchonnage will also be questioned to intervention group participants (Tables 1 and 2).

For the care-recipient the following background characteristics will be collected: age, gender, marital status, ethnicity, region, National Registration Number, educational level, being on a waiting list for long-term nursing home placement, dementia-specific medication use, activities of daily living (Belgian Katz scale), and severity of dementia (GDS). In a later phase, the National Registration Number of the person with dementia will allow us to trace study participants in the IMA database (Intermutualistisch Agentschap) and gather information on resource use and date of placement in a nursing home over a longer time period than the trial (Tables 1 and 2).

### Cost-effectiveness analysis

When appropriate, i.e. if the intervention demonstrates an effect in the study endpoints, within-trial and modeled cost-effectiveness analyses will be conducted in a separate economic evaluation plan [31].

First the analysis will be performed from the perspective of the healthcare payer taking into account direct healthcare costs for the government’s healthcare budget (RIZIV/INAMI) as well as patients’ co-payments [32]. Assuming that policy makers would consider reimbursement of in-home respite care of the Baluchon type in the future, the daily cost of Baluchonnage will be included in the analyses [33]. Alongside the costs of Baluchonnage other costs of healthcare resource use including hospital, residential, and community care will be included [31].

Additionally, also a full societal viewpoint will be undertaken not only including potential direct healthcare costs for the healthcare budget and patients, but also all other direct and indirect costs for caregivers and patients. Because in this viewpoint everyone affected by the intervention should be considered, caregiver time and costs (f.e. time spent in caregiving, productivity loss) as well as resource use and costs of other sectors (f.e. food delivery) should be included.

Based on the KCE guidelines (Belgian Health Care Knowledge Centre) for health economic evaluations in Belgium future costs will be discounted at 3% and future QALY’s at 1.5% [32]. Health utilities or QALY’s of caregivers from both intervention arms will be derived from the Belgian public preference list based on scores on the EQ-5D [34].

Decision analytic modeling will be carried out to extrapolate effects of the intervention found in the trial to a longer time horizon. The model will be based on the results from the trial as well as existing data from literature. Assumptions, hypotheses, and sources of information will be represented in a transparent and clear way. Finally, the model will be validated by experts.

The incremental cost-effectiveness ratio (ICER) will be calculated using the following equitation [34]:$$ \begin{array}{l}\mathrm{ICER} = \underline {\Delta \mathrm{COSTS}}\left( difference\  between\  mean\  total\  cost\  of\  in tervention\  group\  and\  control\  group\right)\\ {}\kern4em \Delta \mathrm{QALYs}\left( difference\  between\  mean\  in\  QALY's\  of\  in tervention\  group\  and\  control\  group\right)\end{array} $$

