**Methods:**

This manuscript described a quasi-experimental study to assess (cost)-effectiveness of an in-home respite care program to support informal caregivers of persons with dementia. Study population: 124 informal caregivers and persons with dementia will be included in the intervention group and will receive an in-home respite care program by an organization called Baluchon Alzheimer. 248 dyads will be included in the control group and will receive standard dementia care. The primary outcome is caregiver burden. Secondary outcomes are: quality of life of caregivers, frequency of behavioral problems of persons with dementia and the reactions of caregivers to those problems, intention to institutionalize the care-recipient, time to nursing home placement, resource use of the care-recipient, and willingness to pay for in-home respite care. When the trial demonstrates a difference in outcomes between both groups, within-trial and modeled cost-effectiveness analyses will be conducted in a separate economic evaluation plan to evaluate possible cost-effectiveness of the in-home respite care program compared to the control group receiving standard dementia care. Finally, the model based cost-effectiveness analyses will allow to extrapolate effects over a longer time horizon than the duration of the trial.

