When the trial demonstrates a difference in outcomes between both groups within-trial and modeled cost-effectiveness analyses will be conducted in a separate economic evaluation plan to evaluate possible cost-effectiveness of the in-home respite care program compared to the control group receiving standard dementia care. Finally, the model based cost-effectiveness analyses will allow to extrapolate effects over a longer time horizon than the duration of the trial.

The specific research questions to be answered are:Is in-home respite care an effective strategy in supporting informal caregivers of people with dementia? Can in-home respite care decrease their burden, improve their reactions to behavioral problems and cause a difference in quality of life of the caregiver?What impact does in-home respite care have on the frequency of behavioral problems of people with dementia?What impact does in-home respite care have on the healthcare system in terms of resource use, intention to institutionalize, and time to nursing home admission?Is in-home respite care a cost-effective strategy in supporting informal caregivers of people with dementia from the healthcare payer and societal perspective compared to no in-home respite care?What are informal caregivers of persons with dementia willing to pay per day for in-home respite care?

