## Methods/design

### Design

A quasi-experimental study is designed to assess the effectiveness of an in-home respite care program on caregivers of persons with dementia. The intervention group will consist of caregiver/care-recipient dyads receiving an in-home respite program called “Baluchonnage” and will be compared to a control group that does not receive this program. Comparison between the groups will be done by collecting health related and economic data.

Eventually, if the intervention is effective, modeled and trial based cost-effectiveness analyses will be undertaken in a separate economic evaluation plan. Analyses will be performed from the perspective of the healthcare payer (RIZIV/INAMI (National Institute for Health and Disability Insurance) and patient) and from a full societal viewpoint. Finally, the model based cost-effectiveness analyses will allow to project effects over a longer time horizon than the duration of the trial. An additional five-years’ time-horizon is chosen based on evidence of the average life expectancy in dementia [15, 16].

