### Statistical analysis

First of all, descriptive statistics will be represented to draw a clear profile of the characteristics of study participants. Therefore the mean, percentages, and the standard deviations of quantitative variables will be displayed. To determine possible baseline differences between the groups, mean values of baseline characteristics will be compared using independent sample t-tests for continuous variables if normally distributed or by performing Pearson’s chi-square test for categorical variables. To help control for bias and confounding, statistical techniques such as propensity score matching will be used. Propensity score matching can be seen as a tool to simulate a RCT setting. In this way we can expect the observed effect to be an unbiased estimate of the real effect [41, 42].

To investigate possible effects of the intervention on the primary and secondary outcomes, analysis of variance will be conducted if the outcome variables are normally distributed. A *P*-value of 0.05 will be considered as significant. All analyses will be based on intention to treat also taking drop-outs into account and avoiding overestimation of respite care effects.

When the intervention is effective a cost-effectiveness analysis in a separate economic evaluation plan will be performed. ICERs will be calculated for the mean and upper and lower confidence levels of the costs and consequences. To explore uncertainty one-way-sensitivity analysis will be conducted around the ICER and illustrated in a Tornado diagram. Additionally, on all input variables a probabilistic sensitivity analysis, also called Monte Carlo analysis, will be conducted to test robustness of the model. These results will also be illustrated. Finally, the results and the willingness to pay threshold of the Belgian Health Care System will be presented in a cost-effectiveness acceptability curve [34].

To compare time to nursing home placement of persons who use respite care to those who do not, we will use Kaplan-Meier survival curves to illustrate association between the comparison groups. By additionally conducting a log-rank test statistical difference between the groups in time to placement can be found [43].

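### The cost-effectiveness analysis runs only if the trial shows an effect, by an undefined trigger, so an unconditional research question can go unanswered

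*Protocol article*

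**What the plan says.** The fourth research question in the Background of the protocol article is put without any condition: "Is in-home respite care a cost-effective strategy in supporting informal caregivers of people with dementia from the healthcare payer and societal perspective", compared with no in-home respite care.

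Five places then make the economic analysis depend on the trial result, in three forms of words:

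- **A difference between the groups.** Abstract, Methods: "When the trial demonstrates a difference in outcomes between both groups, within-trial and modeled cost-effectiveness analyses will be conducted". The Background repeats this almost word for word.
- **Effectiveness.** Design: "if the intervention is effective, modeled and trial based cost-effectiveness analyses will be undertaken". Statistical analysis: "When the intervention is effective a cost-effectiveness analysis in a separate economic evaluation plan will be performed".
- **An effect in the endpoints.** Cost-effectiveness analysis: "if the intervention demonstrates an effect in the study endpoints, within-trial and modeled cost-effectiveness analyses will be conducted".

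None of these names the endpoint, the direction of effect or the threshold. The Statistical analysis section sets 0.05 for the outcome tests but does not link it to this decision.

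The same Cost-effectiveness analysis section defines the ICER from mean differences in costs and QALYs only. It adds: "Decision analytic modeling will be carried out to extrapolate effects of the intervention found in the trial to a longer time horizon". On the horizon, the Design section says: "An additional five-years’ time-horizon is chosen based on evidence of the average life expectancy in dementia".

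**The concern.** A payer wants to know the expected cost and QALY consequences of the programme and how uncertain they are. Significance on caregiver burden, behavioural problems or intention to institutionalize establishes neither. A non-significant burden result is compatible with cost offsets or with a QALY gain. A clear null result for a service costing 65€ + 350€ = 415€ per day (Resource use and costs section) is itself useful for a reimbursement decision.

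The Discussion doubts that EQ-5D is sensitive enough to show an effect over so short a period. It also says that follow-up is short, that placement differences are not expected within it, and that modelling is one of the remedies. Under the condition, that remedy is withheld when the short trial shows no effect, which is where it is most needed.

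Three things are at stake. Question 4 may get no answer. Because the trigger is undefined, whether it has been met can be decided after the results are known. And effects that have first passed a significance test may be carried into a five-year extrapolation.

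**Working it through.** **Inputs.** From the Sample size section: difference 6 ZBI points, SD 15, power 80%, significance level 0.05, drop-out 20%, 124 intervention and 248 control dyads. The sidedness of the test is not stated; two-sided is assumed because it reproduces the plan's figure.

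**Plan's own figure.** n per group = 2 × (1.960 + 0.842)² × 15² / 6² = 98.1, rounded up to 99. Then 99 / 0.8 = 123.75, or 124, and 2 × 124 = 248. Both stated numbers reproduce.

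**Reading A: the trigger is a significant favourable primary outcome (assumption).** SE = 15 × √(1/n₁ + 1/n₂). The critical difference is c = 1.96 × SE. The analysis is skipped with probability Φ((c − δ)/SE), where δ is the true difference. The control number after matching is not stated, so both 99 and 198 evaluable controls are shown.

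| Evaluable dyads | SE | c | Skipped at δ = 6 | at δ = 4.5 | at δ = 3 |
|---|---|---|---|---|---|
| 99 v 99 | 2.132 | 4.18 | 19.6% | 44% | 71% |
| 99 v 198 | 1.846 | 3.62 | 9.9% | 32% | 63% |

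**Reading B: any one endpoint suffices (assumption).** The possible endpoints are burden, EQ-5D, RMBPC frequency, RMBPC reaction, intention to institutionalize, resource use and time to placement. That makes seven, or six without time to placement, for which few events are expected. With no true effect and each test at 0.05:

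- Either direction, independent tests: 1 − 0.95⁶ = 26.5%; 1 − 0.95⁷ = 30.2%.
- Favourable direction only, independent tests: 1 − 0.975⁶ = 14.1%; 1 − 0.975⁷ = 16.2%.
- With equal correlations of 0.3 to 0.7 (assumed; simulated): 27% down to 16% in either direction, and 14% down to 8% favourable only.

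Readings A and B are alternatives. Their percentages do not apply together.

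**Selection of the burden estimate under reading A.** The mean estimate given a significant favourable result is δ + SE × φ((c − δ)/SE) / P(significant).

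- 99 v 99, δ = 6: 6.73, a ratio of 1.12. For δ = 3: 5.52, a ratio of 1.84.
- 99 v 198, δ = 6: 6.36, a ratio of 1.06. For δ = 3: 4.89, a ratio of 1.63.

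These ratios are for ZBI points. The ICER contains no ZBI term, and the article gives no correlation between burden and QALYs or costs, so no such ratio can be computed for the ICER inputs.

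**The case against.** The condition is openly stated, so a reader can see it, and it touches neither the sample size nor the effectiveness analysis. Caregiver quality of life, resource use and willingness to pay are outcomes in their own right, so a negative trial would lose the cost-utility synthesis and the model, not all economic evidence. The Statistical analysis section also plans ICERs at the confidence limits, one-way and probabilistic sensitivity analyses and an acceptability curve. All of this stands, and it limits the damage. But those methods sit behind the same condition, as does the separate economic evaluation plan, so they do not remove it.

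A reader might go further and infer that the economic inputs are selected for being favourable, so that the published economic evidence will be biased towards the programme. The document does not support that as a definite statement, for three reasons:

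- The Abstract and Background wording would also admit an unfavourable difference; only the Design and Statistical analysis wording requires effectiveness.
- QALYs and costs are selected only as far as they are themselves triggering endpoints or correlate with one. If burden says nothing about them, selecting on burden does not distort them.
- That any single endpoint is enough, or that the threshold is 0.05, is a reading of the text. It could equally mean the primary outcome, or all endpoints.

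**Conclusion.** The point holds as a conflict between an unconditional research question and a result-dependent analysis rule whose trigger is undefined and inconsistently worded. Followed as written, the rule can leave question 4 unanswered, because it tests something other than what determines cost-effectiveness.

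The size depends on which reading is meant. With a primary-outcome trigger, the analysis is lost in about 10% to 20% of trials when the planned 6-point effect is real, and in more when the effect is smaller. With an any-endpoint trigger, a programme with no effect sets it off in up to 26-30% of trials, about 14-16% counting favourable results only, and less if the endpoints are correlated.

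Bias in the extrapolated effects is possible but not established. The inflation of 1.06 to 1.12 at a true 6 points applies to burden; for QALYs and costs the amount is unknown. This should be changed, but it does not threaten the primary analysis.

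**What to change.** Delete the condition in the Abstract (Methods), Background, Design, Cost-effectiveness analysis and Statistical analysis sections. State that the within-trial cost-utility analysis will be done whatever the effectiveness result, with point estimates and the joint uncertainty of costs and QALYs, presented through the probabilistic analysis and acceptability curve already planned. Feed the five-year model with the observed effect and its uncertainty, not with an effect that must first be significant. If a condition is kept for the long-term model, name its endpoint, direction and threshold in advance and use the same wording throughout.

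The cost is some extra analysis work if the trial is negative. EQ-5D and RUD data are collected at baseline and six months in both groups in any case (Tables 1 and 2), and the sample size does not change.
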